### Statistical Analysis Plan

The following procedures specify how the predefined outcomes will be analyzed. The analysis will follow an exploratory framework. Although simple, biologically plausible hypotheses have been specified, no formal power calculation was performed. Consequently, results will be interpreted as hypothesis-generating rather than confirmatory.

Feasibility outcomes will be summarized descriptively using proportions, medians, and ranges. Timing of sample returns relative to the predefined collection windows (T0, T1, and T2) will be evaluated by calculating time intervals (in d) between the target and actual return dates. These intervals will be summarized using medians and IQR and compared between delivery groups where appropriate. Reasons for loss to follow-up (eg, no sample returned) will be documented, and analyses will be performed on available cases without imputation of missing data. This analysis will help assess protocol adherence and identify potential logistical barriers in the home-based study model.

To address the previously defined microbiome outcomes, the following statistical approaches will be applied: group comparisons between CS and VD will be performed for each time point (T0, T1, and T2) and longitudinally within participants as well as within groups, using all available paired samples (eg, T0-T1 or T1-T2), where applicable. Alpha diversity metrics (eg, Shannon index and Chao1 richness) will be compared using nonparametric tests (Wilcoxon rank-sum or Kruskal-Wallis test). Beta diversity will be evaluated using permutational multivariate ANOVA based on distance matrices (eg, Bray-Curtis and UniFrac). Visualization will include principal coordinates analysis.

Analyses will follow a 2-level structure, with primary community-level testing and secondary, exploratory taxonomic-level summaries.

Relative abundances of microbial taxa at different taxonomic levels will be summarized descriptively.

Exploratory differential-abundance analyses will be performed using ANCOM-II, a method suitable for sparse compositional data that incorporates its own procedures for controlling false discoveries. Taxonomic-level hypothesis testing will only be performed if community-level analyses indicate meaningful group differences.

Missing data will not be imputed. Samples with insufficient sequencing depth will be excluded from diversity analyses but may be retained for descriptive taxonomic summaries. Sensitivity analyses will be considered to evaluate the robustness of key findings. Sensitivity analyses may include rerunning key comparisons with alternative distance metrics or differential-abundance methods. If imbalances in relevant maternal variables (eg, prevalence of gestational diabetes) are observed between study groups, multivariate statistical models (eg, generalized linear models and redundancy analysis) will be applied to adjust for potential confounding effects. Stratified analyses or subgroup comparisons may also be conducted if sample size permits.

All statistical analyses will be performed in Python, using QIIME 2-compatible plugins (eg, ANCOM-II) and standard scientific Python libraries. Software versions and analysis scripts will be documented for reproducibility.

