**Methods:**

The MAMA (Microbiome Changes Due to Antibiotic Prophylaxis in Mothers at Birth) study is a prospective, 2-arm observational cohort study conducted entirely off-site. Women in the third trimester of pregnancy were recruited at 2 German level-1 perinatal centers and affiliated outpatient facilities. Participants underwent either CS with PAP (single dose cefuroxime 1.5 g intravenously) or VD without antibiotics. Stool samples were self-collected at home and returned by mail at 3 predefined time points: late pregnancy (T0), 2 to 3 days post partum (T1), and 90±10 days post partum (T2). Primary outcomes are feasibility indicators, including recruitment rate, sample and questionnaire return rates at each time point, adherence to sampling windows, and participant retention across follow-up. Secondary outcomes are exploratory microbiome measures based on 16S rRNA gene sequencing (V3-V4), including alpha diversity indices, beta diversity metrics, and relative taxonomic abundances. Microbiome analyses are explicitly compositional and hypothesis-generating. Group comparisons and longitudinal within-individual changes will be assessed using nonparametric diversity metrics and multivariate distance–based methods. No confirmatory hypothesis testing is planned.

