### Data Collection and Sample Handling

Sample collection was performed independently by participants at home as part of the fully remote study workflow. Final group assignment (CS vs VD) was based retrospectively on the actual mode of delivery at birth. Each participant was asked to provide 3 stool samples at predefined time points: during late pregnancy (T0, from gestational week 32 onward), within 2 to 3 days postpartum (T1), and at 90 (±10) days postpartum (T2). These time points were selected to capture baseline microbiome composition, immediate peripartum changes, and long-term recolonization dynamics. For each time point, participants received a sample collection kit that included a collection tube (DNA/RNA Shield Fecal Collection Tube, Zymo Research), a single-use stool catcher (Feces Catcher, Zymo Research), written instructions, and a prepaid return envelope. Paper-based questionnaires accompanied each sample kit and covered maternal health status, medication use, pregnancy and birth-related variables, and lifestyle factors such as nutrition and physical activity. Participants returned both the stool sample and completed questionnaire in the same shipment. Questionnaires were designed to be completed within approximately 10 minutes and spanned 2 to 3 pages, depending on the time point. Incomplete or missing forms were actively followed up by the study coordinator.

Samples were shipped by standard postal service and received by the coordinating study center. Although the exact time between sampling and mailing was not recorded for all participants, no sample exceeded the manufacturer’s recommended stability window.

Upon arrival, samples were documented and immediately stored in a temperature-monitored, alarm-secured refrigerator at 4°C to 8 °C, where they remained until DNA extraction. The median storage duration was 434 days (range: 137‐784 d), with no deviations from the defined storage conditions. Despite the stabilizing effect of DNA/RNA Shield, the wide range of storage periods may still cause subtle bias.

The nucleic acid stabilization buffer (DNA/RNA Shield) ensures preservation of microbial DNA for at least 24 months at ambient temperature (4° C‐25  °C) and indefinite stability when frozen (<−20 °C), according to the manufacturer. Accordingly, all returned samples were accepted for processing. No exclusions were made due to transport delays, damage, or temperature fluctuations.

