### Outcomes

The primary outcomes of this protocol are feasibility indicators that assess the performance of the fully remote study design. These include the proportion of contacted women who enrolled; sample and questionnaire return rates at T0, T1, and T2; timeliness of sample returns relative to the predefined sampling windows; and overall participant retention across study time points. Together, these measures evaluate compliance, protocol adherence, and the suitability and scalability of the decentralized workflow for maternal microbiome research.

Microbiome-related outcomes are exploratory and focus on compositional rather than absolute changes in microbial communities, as 16S rRNA-sequencing yields relative abundances. These outcomes include alpha diversity metrics (eg, Shannon index and Chao1 richness), beta diversity metrics (eg, Bray-Curtis dissimilarity, and weighted and unweighted UniFrac distances), and relative abundances of bacterial taxa across taxonomic levels from phylum to genus with ASV-level feature tables used for technical analyses. Exploratory identification of marker taxa may be performed where feasible. No diagnostic or clinical interpretations of “dysbiosis” will be drawn.

In line with the observational design and modest, imbalanced sample size, all hypotheses are nonconfirmatory and serve to guide hypothesis-generating analyses. We hypothesize that women undergoing CS with PAP will exhibit a transient reduction in alpha diversity at T1 compared to VD; that compositional perturbations at T1 will at least partially resolve by T2; and that the relative abundance of *Clostridioides difficile* will be higher at T1 in the CS group than in VD. These hypotheses reflect biologically plausible patterns without implying confirmatory testing.

Exploratory analyses will consider associations between microbiome features and maternal metadata such as parity, medication intake, and dietary patterns, where feasible. Subgroup analyses may be limited by sample size constraints, and residual confounding is expected.

Outcomes will be described both cross-sectionally (CS vs VD at each time point) and longitudinally (across T0→T1→T2 within individuals as well as within groups). The statistical procedures for these analyses are outlined in the subsequent section.

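### The planned timeliness interval has no target date at T0, and at T1 and T2 it describes returned samples only, so it does not directly measure adherence to the sampling windows

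*Protocol article*

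**What the plan says.** The Abstract (Methods) lists among the primary outcomes "adherence to sampling windows, and participant retention across follow-up". The Outcomes section lists return and timing as separate indicators: "sample and questionnaire return rates at T0, T1, and T2; timeliness of sample returns relative to the predefined sampling windows".

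The Statistical Analysis Plan section says that timing at T0, T1 and T2 "will be evaluated by calculating time intervals (in d) between the target and actual return dates". It continues: "These intervals will be summarized using medians and IQR and compared between delivery groups where appropriate". It also states that "analyses will be performed on available cases without imputation of missing data", and that reasons for loss to follow-up will be documented. A general sentence precedes this: "Feasibility outcomes will be summarized descriptively using proportions, medians, and ranges".

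The windows are given in Data Collection and Sample Handling: "during late pregnancy (T0, from gestational week 32 onward), within 2 to 3 days postpartum (T1), and at 90 (±10) days postpartum (T2". T2 has a nominal day and a tolerance. T1 is a two-day range. T0 has a start but no target day, and no stated end.

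The note to Figure 2 (Results) defines a per-protocol sample by receipt inside the window, and treats collection outside the windows as a protocol deviation.

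**The concern.** The summary chosen does not match the outcome it serves.

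- **T0.** A distance from target needs a target. If one is chosen after the data are in, the T0 result depends on that choice, and so does the comparison between delivery groups. The Discussion (Principal Findings) reports that timely collection at T0 and T1 was hard to secure in the vaginal delivery group, so T0 timing may well differ by group.
- **T1 and T2.** A woman who returns nothing has no interval and drops out of the summary.
- **Median and IQR against a window.** Adherence to a window is a yes/no property of each expected sample. A median and IQR describe where the middle of the returned samples lies, not how many met the window.

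The article already concludes that feasibility is demonstrated, and the main results paper is still to come. A reader of that paper could take a favourable median interval as evidence of adherence when it speaks only for the samples that came back.

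**Working it through.** **Inputs.** Enrolled: 37 (25 cesarean, 12 vaginal), from Results. Women with at least one sample: 31 (20 and 11), from Table 1. Analysed per time point: T0 31, T1 19, T2 21, from the Figure 2 note. Windows: Data Collection and Sample Handling.

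**Reproducing the article's totals.** 31 + 19 + 21 = 71, as stated. 25 + 12 = 37 and 20 + 11 = 31, also as stated. The article gives no timeliness figure to reproduce.

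**T0.** Assume birth at 37 to 41 weeks, a range the article does not give. The window from week 32 to delivery is then (37 − 32) × 7 = 35 days to (41 − 32) × 7 = 63 days long. A sample taken at week 36 is 28 days late against a week-32 target and 28 days early against a week-40 target. The article supplies neither target.

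**T1 and T2: response to non-return.** Take 19 illustrative intervals and vary the number enrolled. The last two columns rank unreturned samples as latest.

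| Enrolled | Planned median, prompt set | Planned median, slow set | Non-return ranked latest, prompt set | Non-return ranked latest, slow set |
|---|---|---|---|---|
| 19 | 5 | 16 | 5 | 16 |
| 25 | 5 | 16 | 7 | 24 |
| 31 | 5 | 16 | 9 | 26 |
| 37 | 5 | 16 | 10 | 30 |
| 60 | 5 | 16 | not observable | not observable |

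The planned median is constant down each column, so it is blind to non-return. It does separate prompt from slow returns.

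With 37 women the median is the (37 + 1)/2 = 19th value. If the analysed counts stood for returned counts and missing samples ranked latest, this would be the longest of the 19 intervals at T1 and the 19th of 21 at T2. The upper quartile, rank 0.75 × 38 = 28.5, could not be observed at either time point.

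**T2: median and IQR against the window.** Take 21 returned samples as an illustration, with signed deviations from day 90:

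- five at −12 days, eleven at −5, −4, …, +5, and five at +12 days;
- median 0;
- quartiles at the 6th and 16th values: −5 and +5;
- quartiles at ranks 5.5 and 16.5 instead: (−12 − 5)/2 = −8.5 and (5 + 12)/2 = +8.5.

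Both quartiles lie inside ±10, yet 10/21 = 48% of samples are out of window. The article does not say whether intervals are signed. With absolute deviations the same data give a median of 5 and an upper quartile (16th value) of 12, which would show the problem. In that case about 5/21 = 24% could lie outside with the upper quartile still inside.

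**Proxy for the size here (Wilson 95% CIs).**

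| | Of 37 enrolled | Of 31 with any sample |
|---|---|---|
| T1 | 19/37 = 51.4% (35.9 to 66.6) | 19/31 = 61.3% (43.8 to 76.3) |
| T2 | 21/37 = 56.8% (40.9 to 71.3) | 21/31 = 67.7% (50.1 to 81.4) |

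Without an analysed sample: 37 − 19 = 18 at T1 and 37 − 21 = 16 at T2. These are analysed counts, not returned or in-window counts.

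**The case against.** The strongest reply is that the indicators are meant to be read together. Return rates at each time point and retention are primary outcomes in their own right, reasons for loss are documented, and an interval among returned samples is conditional on return by its nature. This stands: non-return is not hidden from the study.

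A reader might infer that the median will look good however many samples are lost, or that it cannot show poor adherence. The documents do not support that. Late returns worsen the median, as the slow set shows. Because the interval runs to the return date, the mailing delays reported in Principal Findings push it towards looking late.

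Nor is the median with IQR the only summary the plan allows. The general sentence on feasibility outcomes mentions proportions and ranges. Ranges would show extreme values, and proportions could include an in-window proportion. The timing paragraph, however, does not name one.

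The cancellation argument is limited to T2 and to signed intervals. At T1 an early sample can deviate by only about two days, so it cannot offset a long delay.

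The counts of 19 and 21 are also reduced by exclusions for antimicrobial use, which concern neither return nor timing.

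Finally, a condensed article may leave a T0 target to a fuller document. But this article states both the calculation and the window, and the two do not fit together.

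**Conclusion.** The point holds in a limited form. At T0 the interval is undefined as written. At T1 and T2 it is conditional on return and does not change with the number of samples never returned. It is therefore an indirect measure of the primary outcome of window adherence. At T2 a median and IQR inside the window are compatible with nearly half of returned samples lying outside it, assuming signed intervals and the illustrative 21 values above.

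The article does not allow the actual effect to be sized. The shares of 51% at T1 and 57% at T2 show that missing or excluded samples are numerous enough to matter. True return rates could be higher, and the 21-value illustration is no statement about the 21 samples analysed. No microbiome result is affected. The change is worth making before the results paper but does not threaten the study.

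**What to change.** 1. **T1 and T2.** By actual mode of delivery, report the number and proportion of all enrolled women (37) whose sample fell inside the window, with 95% CIs. Count non-return and out-of-window samples as not adherent. Give the same figures over the 31 women with at least one sample. Use the in/out classification already made for Figure 2, and state whether it rests on collection or receipt, since the figure note uses both. List exclusions for antimicrobial use separately.
2. **Return rates.** Keep them as a separate outcome, because non-return and late return point to different logistical problems.
3. **Median and IQR.** Keep them, labelled as among returned samples. Say whether deviations are signed or absolute, and which T1 day is the reference.
4. **T0.** Remove it from the target-interval analysis. Report whether the sample was collected from week 32 and before delivery (yes/no), with gestational age at collection.

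The cost is a few sentences and one table, largely from a classification that exists. There are two downsides. The adherence figure may look less favourable than a median interval. Status by collection date may also be unknown for some women, because the time from sampling to mailing was not recorded for all; state the number unknown.

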Analyses will follow a 2-level structure. First, community-level analyses where ASV-based distance matrices (Bray-Curtis, and weighted and unweighted UniFrac) will be used to assess group differences via permutational multivariate ANOVA [30]. Longitudinal microbiome changes will be evaluated by comparing within-individual distance differences across time intervals using Mann-Whitney *U* tests, visualized via principal coordinates analysis. Second, taxonomic-level analyses, in which higher-rank taxonomic profiles (phylum, genus, and species, where available) are summarized descriptively. Hypothesis testing at the taxonomic level will only be conducted if community-level differences emerge, to avoid overinterpretation of sparse compositional data. Given the modest cohort size, all analyses are designed for hypothesis-generating, exploratory interpretation.

Alpha diversity (Shannon index, observed features, and Faith phylogenetic diversity) and beta diversity (Bray-Curtis, and weighted and unweighted UniFrac) will be calculated to describe within- and between-sample diversity. Group comparisons will be analyzed using the Wilcoxon rank-sum or Kruskal-Wallis tests for alpha diversity and permutational multivariate ANOVA for beta diversity. Differential-abundance analysis will be performed using the Analysis of Composition of Microbiomes II (ANCOM-II) [31], a method developed for sparse compositional microbiome data. Given the modest sample size, differential-abundance findings will be interpreted exploratorily. All downstream analyses and visualizations will be performed in QIIME2 and a Python-based environment (Python Software Foundation). Workflow steps, parameters, and software versions will be version-controlled to ensure reproducibility. In addition to taxonomic data, analyses will integrate metadata on parity, medication use, and dietary habits. Associations between microbiome composition and clinical, lifestyle, or sociodemographic variables will be explored through correlation analyses and, where applicable, multivariate approaches such as redundancy analysis or generalized linear models.

Although DNA/RNA Shield stabilizes microbial nucleic acids, prolonged refrigerated storage before extraction may introduce subtle compositional shifts. This potential source of bias will be considered during interpretation.

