**Figure 2. F2:**
[figure not shown]
Flowchart of participant enrollment, allocation, follow-up, and analysis in the MAMA (Microbiome Changes Due to Antibiotic Prophylaxis in Mothers at Birth) study, in line with the STROBE (Strengthening the Reporting of Observational Studies in Epidemiology) recommendations for observational studies. CS: cesarean section; VD: vaginal delivery.

A per-protocol sample was defined as a stool sample received within the prespecified time window and passing quality control. Protocol deviation was defined as exclusion from the per protocol set due to intake of antimicrobial agents (antibiotic or antifungal) other than the study medication or as sample collection outside the defined protocol windows and could not be assigned to a valid time point. Two women, who were initially allocated to the vaginal delivery group, delivered by CS and were therefore analyzed in the CS group; these women are counted under vaginal delivery at baseline (T0) and under CS at follow-up (T1 and T2). Numbers reported per group reflect participants analyzed at each time point; totals across groups were: T0 (n=31), T1 (n=19), T2 (n=21), and final analysis (N=71).

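### Change over time within the same women is planned on paired samples, but only independent-sample rank tests are named

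*Protocol article*

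**What the plan says.** Under Outcomes, results are to be described by delivery group at each time point and also "longitudinally (across T0→T1→T2 within individuals as well as within groups"), and the reader is referred to the next section for the procedures.

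That section, the Statistical Analysis Plan, commits to CS versus VD comparisons at each time point and to comparisons "longitudinally within participants as well as within groups, using all available paired samples (eg, T0-T1 or T1-T2), where applicable". The only tests it names for alpha diversity follow: "Alpha diversity metrics (eg, Shannon index and Chao1 richness) will be compared using nonparametric tests (Wilcoxon rank-sum or Kruskal-Wallis test").

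Under Microbiome Analysis and Bioinformatics Pipeline, the same two tests are tied to the delivery-group contrast: "Group comparisons will be analyzed using the Wilcoxon rank-sum or Kruskal-Wallis tests for alpha diversity". Longitudinal change is to be evaluated by "comparing within-individual distance differences across time intervals using Mann-Whitney" U tests.

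The article names no signed-rank test, Friedman test, mixed model or other paired method. The text below Figure 2 gives the analyzed samples as "T0 (n=31), T1 (n=19), T2 (n=21), and final analysis (N=71").

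**The concern.** Rank-sum, Mann-Whitney U and Kruskal-Wallis all treat the observations as independent. Repeated samples from one woman are not. If her values correlate positively over time, an unpaired test charges the stable between-woman differences to error. It then rejects too rarely under no change and has less power when change is real. T0-T1 and T1-T2 distances from the same woman also share the T1 sample, so testing one set against the other as two independent samples has the same fault.

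The data are few: T1 has 19 samples over both groups. One stated hypothesis concerns change over time, namely partial resolution of the T1 shift by T2. An over-conservative test would tend to leave such change undetected, in a study whose stated use is to inform later, powered work.

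**Working it through.** **What the article supplies.** No power, alpha, effect size, SD or within-woman correlation is given ("no formal power calculation was performed"), so there is no power figure to reproduce. The one checkable sum agrees: 31 + 19 + 21 = 71. Because T1 has 19 samples, there are at most 19 T0-T1 pairs, 19 T1-T2 pairs and 19 complete triplets over both groups. Counts of pairs per group are not in the readable text (Figure 2 is not shown).

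**Assumptions.** Two-sided alpha 0.05; normal scores; shift d of 0.5 or 0.8 between-woman SD; within-woman correlation ρ from 0 to 0.7; 19 pairs as the upper bound.

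**Direction.** For n pairs with common variance σ², the difference between time-point means has variance 2σ²(1−ρ)/n, but an unpaired test assumes 2σ²/n. Its null z-statistic therefore has SD √(1−ρ), and its true level is about 2Φ(−1.96/√(1−ρ)): 0.019 at ρ = 0.3, 0.006 at ρ = 0.5 and 0.0004 at ρ = 0.7. At ρ = 0 it is 0.05.

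**Simulation, 19 pairs, 10,000 runs per scenario (rank-sum / signed-rank).**

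| ρ | rejection under no change | power, d = 0.5 | power, d = 0.8 |
|---|---|---|---|
| 0 | 0.046 / 0.049 | 0.30 / 0.29 | 0.64 / 0.63 |
| 0.3 | 0.021 / 0.046 | 0.26 / 0.39 | 0.65 / 0.78 |
| 0.5 | 0.008 / 0.049 | 0.25 / 0.52 | 0.69 / 0.90 |
| 0.7 | 0.001 / 0.050 | 0.20 / 0.74 | 0.72 / 0.99 |

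A separate simulation gave 26% vs 38%, 26% vs 51% and 21% vs 74% for d = 0.5 at ρ = 0.3, 0.5 and 0.7, so the figures are good to about one percentage point.

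**Relative loss, 1 − unpaired/paired (from unrounded powers).**
- d = 0.5: 1 − 0.257/0.394 = 35%; 1 − 0.247/0.521 = 53%; 1 − 0.205/0.737 = 72% at ρ = 0.3, 0.5, 0.7.
- d = 0.8: 1 − 0.651/0.778 = 16%; 1 − 0.688/0.897 = 23%; 1 − 0.724/0.987 = 27%.

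**Fewer pairs.** With 12 pairs, as an illustration of a single group, power at d = 0.5 is 0.16 / 0.23, 0.13 / 0.31 and 0.10 / 0.49 at ρ = 0.3, 0.5, 0.7. Absolute power falls under either test.

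**Unpaired test on all 31 T0 and 19 T1 samples.** The extra T0 samples recover part of the loss: at d = 0.5, 0.36 against 0.41, 0.34 against 0.53 and 0.33 against 0.75 for 19 pairs tested by signed-rank.

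**Three time points.** Kruskal-Wallis against Friedman, 19 women, shift of 0.5 SD at T1 only, 3,000 runs: 0.29 / 0.24 at ρ = 0, 0.24 / 0.33 at 0.3, 0.20 / 0.46 at 0.5 and 0.14 / 0.67 at 0.7.

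**Sample-size equivalent.** For 80% power at d = 0.5, the unpaired comparison needs 2(1.96 + 0.842)²/0.5² = 62.8, so 63 per time point. The paired one needs (1−ρ) times that: 44, 32 or 19 pairs at ρ = 0.3, 0.5 or 0.7.

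**The case against.** The named tests have a valid reading. The governing sentence in the Statistical Analysis Plan has CS versus VD as its subject, and the bioinformatics section assigns the rank tests to group comparisons. Mann-Whitney on one distance per woman, CS versus VD, is also valid. No sentence expressly assigns rank-sum to T0 against T1 in the same women, and a condensed article may leave detail to a fuller plan. This stands as far as it goes, and it confines the point to comparisons over time. It does not remove it: a comparison over time within one group cannot be a CS versus VD contrast, and the section to which Outcomes refers for these procedures names no test that fits paired samples.

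The consequence is also limited. The analyses are exploratory, the Limitations section already warns that small or moderate effects cannot be reliably detected, and two of the three stated hypotheses (alpha diversity and *C. difficile* at T1) are CS versus VD contrasts. That stands, and it bears on the grade.

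A reader might infer more than the article supports:
- **Most of the power is lost.** This holds only for a moderate shift with ρ of about 0.5 or more. At 0.8 SD with 19 pairs the loss is about a quarter or less, and at ρ = 0 there is none.
- **The T1-T2 distance is the plan's measure of resolution.** The article never says so; its example pairs are introduced as examples and do not exclude T0-T2.
- **Repeated samples will be permuted freely in the permutational ANOVA.** No permutation scheme is stated. With one sample per woman at a time point, free permutation is correct.

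**Conclusion.** The point holds for comparisons over time within the same women, including T0-T1 against T1-T2 distances. The article specifies paired data there and offers only independent-sample tests. If those tests are applied, the true level falls to about 2%, 1% and 0.1% at ρ = 0.3, 0.5 and 0.7. The relative power loss with at most 19 pairs is about 35% to 72% for a 0.5 SD shift and 16% to 27% for 0.8 SD over that range. These sizes rest on the assumed correlation, shift, normal scores and alpha; only the ceiling of 19 pairs comes from the article.

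The CS versus VD tests are sound. The primary feasibility outcomes are untouched. The error is a conservative one. This should be fixed before the results are reported, but it does not undermine the study.

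**What to change.** 1. Keep rank-sum/Mann-Whitney for CS versus VD at each time point, and for CS versus VD on each woman's change or within-individual distance. Say explicitly that this is what those tests compare.
2. For change over time within a group, and for comparing intervals within the same women, name the Wilcoxon signed-rank test on pairs and Friedman for complete triplets. A mixed model with a random intercept per woman is an option that can use all 71 samples.
3. State how the two women counted as VD at T0 and as CS at T1 and T2 (text below Figure 2) are grouped in any within-group or group-by-time analysis.
4. As an addition for the hypothesis of partial resolution by T2, report for each woman distance(T0,T2) minus distance(T0,T1). A negative value means she is closer to her baseline at T2 than at T1.

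The cost is a few sentences and a few lines of code. No new data are needed, and the article describes the analyses as still ongoing in December 2025. If results have been seen by then, the change should be recorded as made after that point.
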